#### Secondary outcome measures

##### Personal recovery dimensions

Two additional measures will be included for more focused measurement of specific personal recovery dimensions targeted by the intervention. Hope and optimism will be measured by the Schizophrenia Hope Scale, a validated 9-item self-report scale on which items are scored *disagree*, *agree* or *strongly agree* [59]. Social connectedness will be indexed by version 3 of the UCLA Loneliness Scale [60], the most widely used measure of loneliness versus connection with others, which comprises 20 items which are self-rated on a 4-point response scale from *never* to *always*. The total scores on each of the measures will be used in analyses.

##### Psychotic symptoms

Psychotic symptom severity will be measured by the PANSS [61]. The PANSS is a standardised interview-based measure of schizophrenia symptomatology widely used in treatment trials. It comprises seven items assessing positive symptoms, seven assessing negative symptoms and 16 items assessing general symptoms. The PANSS total score is used as part of the randomisation stratification, and the total and subscale scores will be analysed as secondary outcomes. Inter-rater reliability on the PANSS is checked every 3–6 months by research assistants co-rating face-to-face assessments, with recalibration of ratings occurring if necessary.

Although the PANSS has become a standard in psychosis treatment research, it has been criticised for providing a relatively indirect and insensitive index of the impact of psychosocial interventions on psychosis symptoms, where the impact of psychosis on distress and functioning is the key target, rather than symptom severity per se [8, 62]. Hence, the impact of psychotic symptoms will be measured by the Subjective Experience of Psychosis Scale (SEPS [63]). This is a psychometrically validated [63] questionnaire on which participants rate the current impact of psychotic symptoms on various aspects of distress, day-to-day functioning and subjective experience identified as important by mental health service users. The negative impact of psychosis is measured by the total of 29 5-point (*not at all* to *very much negative*) items. The SEPS is completed only by participants who have experienced psychotic symptoms in the week prior to the baseline assessment.

##### Emotional symptoms

Emotional symptoms will be measured using the 21-item version of the Depression Anxiety Stress Scale (DASS-21, [64]), which consists of 3 subscales (Depression, Anxiety, Stress) comprising items rated on a 4-point scale of the extent to which the experience occurred over the past week from 0 (*did not apply to me at all*) to 3 (*applied to me very much or most of the time*). The DASS-21 is validated and psychometrically robust [64].

##### Quality of life

Quality of life will be measured using the Assessment of Quality of Life (AQoL)-8D [65] consisting of 35 items across eight dimensions comprisingphysical (independent living, pain, senses) and psychosocial (mental health, happiness, coping, relationships, self-worth) dimensions of quality of life. The AQoL-8D is comprehensively validated and demonstrates high test-retest reliability [66]. The AQoL-8D total and physical and psychosocial scores will be used as a secondary outcome, and the utility scoring algorithm will be used to derive quality adjusted life years (QALYs) for an economic analysis which will integrate these data with those from other studies in the research program and be reported upon separately.

##### Collaboration with mental health services

We will also examine whether there are indirect effects of the intervention on the working relationship with the person’s usual services. This will be assessed using the Scale to Assess Therapeutic Relationships in Community Mental Health Care (STAR) Patient Version [67], a psychometrically validated self-report scale with 12 items on positive collaboration, positive clinician input, and non-supportive clinician input each rated from 0 (*never*) to 4 (*always*).

##### Subjective experience of intervention

At the three month assessment point, all participants complete questions asking “Overall, did the website make you feel better, or worse, or no different?” and “Do you feel that using the website made the impact of your mental health problems better, or worse, or no different?”, both answered on a 5-point scale ranging from *much worse* to *much better*. As well as providing an index of the subjective perceived benefit of the interventions, this measure will be used to assess for any perceived adverse effects. Although not a formally validated measure, analogous questions have proved sensitive to treatment condition in two previous trials of psychosis [55, 56]. In addition, a sample of SMART participants will be invited to take part in more detailed qualitative interviews about their experiences of the intervention, which will be reported upon separately.

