Sessions involve use of the website to stimulate discussion about self-management and recovery. The worker has the following roles: (a) using website material to encourage the participant to reflect upon their own recovery, (b) facilitating the participant forming intentions to make changes on the basis of what has been discussed, (c) promoting familiarity with the site to independently use its features, and (d) encouraging the participant to use the site between sessions. The initial session includes orienting the participant to both the website and the concept of personal recovery. Participants are provided with their own login to the SMART website, and are introduced to the navigation, supported by a video on the site. This is followed by videos on the concept of personal recovery, and discussion about different material included in the website. This is used to identify priorities in the material for the therapist and participant to look at in subsequent sessions. In subsequent sessions, the worker and participant identify the area they want to focus on, with the core of the session involving a process of viewing website material together, using this as a prompt for discussion about the participant’s own recovery, and an invitation to complete reflective exercises on the site and/or make public posts about the content if willing. These sessions begin with a review of reflections since the last meeting, and any content which the person has used, and conclude by considering any changes the person would like to enact, and planning ongoing use of the site during the week.

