### Befriending

Participants in the comparison condition receive sessions based upon a neutral social contact, involving shared activity and discussion about non-mental health topics such as current affairs, recent events and activities in the participant’s life, and the participant’s interests. This is a manualised intervention, the structure of which is based upon the befriending protocol of Bendall et al. [52], a credible and acceptable comparison condition [53], which has been used as a control condition to match for therapist time in a number of psychosocial intervention trials [54–56]. In this trial the standard protocol is augmented by use of the tablet computer to browse Internet sites related to participants’ interests, and as a potential means of facilitating discussion. This comparison condition was selected to provide a control for both therapist time, and for engagement in the use of technology.

In both groups, interventions are continued until, (a) all eight sessions are completed, (b) the end of the three month therapy delivery window is reached, or (c) the participant chooses to withdraw. If participants experience significant distress or deterioration in their mental state, researchers remind participants of their right to withdraw, and encourage them to make an informed choice about their ongoing participation. If participants wish to discontinue intervention sessions, they are still followed up for assessment if willing to do so.

Participant adherence to protocols will be monitored through records of session attendance. In secondary analyses, attendance of at least four sessions will be considered as the threshold for receiving a minimum dose of the intervention. Workers attend weekly supervision led by NT to ensure protocol fidelity. Worker fidelity will be further assessed by a researcher blind to participant allocation listening to a random sample of audio recordings of sessions, and being asked to allocate sessions to condition.

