### Allocation and blinding

The trial uses minimisation randomisation, conducted using the software Minimpy (http://sourceforge.net/projects/minimpy). This generates random allocations based on the stratification parameters for each participant enrolled in the study. The randomisation procedure and setup of the Minimpy parameters was prepared by the study statistician to stratify by type of mental health service the person receives (clinical vs community sector vs both), symptom severity (Positive and Negative Syndrome Scale (PANSS) total ≥ vs < 67), and frequency of Internet use (daily vs less than daily). Following commencement of the trial, the software is operated by a person independent of the research team, who receives participant codes from the research team as each baseline assessment is completed, runs the allocation, and advises of allocations via return email.

Research staff conducting assessments are blind to participant allocation throughout the study. Participants are unavoidably aware of the conditions they have been randomised to. To reduce expectancy effects for superiority of the intervention over the control condition, the trial was framed as a comparison between two ways of integrating technology into mental health service delivery, with a *health* condition using technology to discuss mental health recovery, and a *social* condition using technology to support discussion about the person’s interests. To maintain assessor blinding, participants are regularly reminded not to divulge their allocated condition or any details of their intervention to assessment staff, as are their mental health workers. Breaches in blindness are recorded and addressed by changing the rater whenever possible. Blindness is also assessed at each assessment following the intervention by asking raters to nominate a guessed treatment condition for the participant and to indicate their level of confidence. The principal investigator (NT) and project manager (FF) are not blinded, and respond to any clinical and research issues during the trial that require knowledge of a participant’s’ condition.

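### The two perceived-benefit and perceived-harm items ask both arms about a website that only SMART is described as having, so the arms rate different things

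*Protocol article*

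**What the plan says.** All passages are in the protocol article.

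- **Who answers, and what is asked.** Under Subjective experience of intervention, at three months "all participants complete questions asking “Overall, did the website make you feel better, or worse, or no different". The second item reads "Do you feel that using the website made the impact of your mental health problems better, or worse, or no different". Both use a five-point scale from much worse to much better.
- **Stated uses.** The measure is introduced with "As well as providing an index of the subjective perceived benefit of the interventions", interventions being in the plural, and the text adds that "this measure will be used to assess for any perceived adverse effects". The choice is supported by the remark that "analogous questions have proved sensitive to treatment condition in two previous trials of psychosis". The same section concedes that the measure is not formally validated.
- **SMART.** Sessions are built around the SMART website. "Participants are provided with their own login to the SMART website".
- **Befriending.** This is neutral social contact on topics other than mental health, "augmented by use of the tablet computer to browse Internet sites related to" the participant's interests. No study website is described for this arm.
- **Blinding.** "Research staff conducting assessments are blind to participant allocation throughout the study". Participants are reminded not to disclose their condition or details of the sessions.

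**The concern.** An item can compare two arms only if it has the same object in both. Here the items name one component, a website, which the document describes for one arm only. A Befriending participant may answer about the sites browsed, about the sessions, or about nothing in particular, and the data will not show which. A SMART participant is asked about the site and not about the meetings with the worker, although Aims describes the intervention as a blend of the two.

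Two readings are at stake. A difference in perceived benefit would mix any real difference with the difference in what was rated. A low count of worse answers in Befriending could also be taken as reassurance about an intervention on which those participants were not clearly asked to comment.

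**Working it through.** **The plan's own figure.** The only design figure is the recruitment target of 148 (Participants: d = 0.5, α = .05, 80% power, 15% attrition; two-sided testing is my assumption). Per arm, n = 2(1.96 + 0.84)²/0.5² ≈ 63, so 126 in total, and 126/0.85 = 148.2. The target reproduces to rounding. The point does not depend on it, but it gives the number affected: 148/2 = 74 in Befriending under 1:1 allocation, and 74 × 0.85 = 62.9 if all the planned attrition had occurred by three months.

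**The passages side by side.**

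| Element | SMART | Befriending |
|---|---|---|
| Study website described | Yes, with personal login | None |
| Other web use described | Not specified | Browsing sites of personal interest |
| Object of the two items | The SMART website | Undefined |
| Sessions rated by the items | No | No |
| In-depth interviews on the experience | A sample | Not described |

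1. The items go to all participants, and no alternative wording for Befriending is given.
2. The stated purpose covers both interventions. The justification by sensitivity to treatment condition implies a between-arm reading.
3. Aims says the comparator explores digital resources unrelated to recovery, so Befriending participants are not meant to be using the SMART site.
4. From 1 to 3, the object rated differs by arm while the intended use needs it to be the same.

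**Other routes for harm.** Serious adverse events are recorded and compared in both arms. The DASS-21 is collected in both arms at 3, 6 and 9 months, as is the SEPS for those with psychotic symptoms in the week before baseline. These scales measure state; they do not ask the participant whether the intervention made things worse. Among the participant-rated items described, only the two website items do that.

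**Illustration on assumed values only.** Suppose both arms truly gave an equal perceived benefit of 0.5 SD, and a share f of Befriending participants answered no different because they had no website to rate. The spurious difference in favour of SMART is 0.5 × f SD. With 62.9 per arm, the SD held at 1 and a two-sided 5% test, the chance of a significant result favouring SMART is Φ(0.5f·√(62.9/2) − 1.96):

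| f | Spurious difference (SD) | Chance of significance |
|---|---|---|
| 0.25 | 0.125 | 10% |
| 0.50 | 0.25 | 29% |
| 1.00 | 0.50 | 80% |

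The document gives neither f nor the 0.5 SD. Other assumptions reverse the sign: for example, Befriending participants might rate sites they chose and enjoyed, while SMART participants who valued the worker gave the site a low rating. The table shows that wording alone could matter. It does not estimate how much it does.

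**The case against.** **Condensed article.** Table 1 appears to list this instrument as Therapy Evaluation, and the section heading speaks of the intervention, so the actual form may carry an arm-appropriate version. That cannot be excluded. But the article gives the item wording in full and assigns it to all participants, so the text as it stands has the mismatch.

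**Uninterpretable?** A reader might infer that the arm comparison is worthless, or that Befriending answers must drift to the scale midpoint. The document does not support either. Befriending participants did use web content, and the trial was presented to participants as two ways of integrating technology, so some could give a meaningful answer about their browsing. There are no response data. SMART answers remain usable as ratings of the website and, because the sessions centre on it, as an imperfect proxy for the sessions.

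**Harm missed altogether?** A reader might also infer this. It goes too far, because the DASS-21, the SEPS and serious adverse events cover both arms. What stands is the narrower gap: harm that participants themselves attribute to the intervention, chiefly in Befriending.

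**Unblinding?** A puzzled remark or a blank answer could hint at allocation to a rater at the three-month visit. The document does not show that this happens. The wording is identical in both arms, a five-point rating does not reveal the arm, and the mode of administration is not stated. Allocation and blinding already provides for reminders, recording of breaches, change of rater whenever possible, and collection of raters' guesses. It is a possible side risk and no more.

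**Importance.** This is a two-item secondary measure with no formal test specified for it. That stands, and it limits the weight of the point.

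**Conclusion.** The point holds in a limited form. As written, the two items have different objects in the two arms and rate the sessions in neither, so a between-arm difference on them is confounded by the wording. They are also the only described items asking participants to attribute worsening to the intervention, and they suit Befriending poorly.

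The measure is affected for the whole comparison arm: 74 planned, about 63 if 15% attrition applied fully by three months. The direction and size of any bias cannot be determined from the document. The QPR, as primary outcome, is unaffected. The conclusion assumes that the printed wording is the wording used in both arms, and that Befriending participants were not given the SMART site; the second assumption is an inference from Aims, SMART and Befriending.

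**What to change.** - Word both items neutrally and identically for both arms, for example by asking about the sessions you had in this study.
- Keep a website-specific item for SMART only, reported as a rating of the site.
- Have participants complete the form themselves, out of the blinded rater's sight.
- Flag answers given under the old wording and do not interpret them as a like-for-like comparison of arms.
- If an arm-appropriate Befriending version is already in use, state it in the protocol; the rewording would then be unnecessary to the extent that it already asks about the sessions.

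The cost is a minor amendment to one form. Registration took place during recruitment, so some participants may already have answered; the drawback is two wordings in the data and fewer participants with the common one.

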##### Serious adverse events

In line with the Australian National Statement on Ethical Conduct in Human Research [68], in the context of this trial serious adverse events include events that lead to participant death, or that are life-threatening, require inpatient hospitalisation, or result in persistent or significant disability/incapacity. During the trial, potential serious adverse events are recorded, and are reviewed to determine whether they are likely to be related to interventions used in the trial. Analysis of outcomes will include a comparison of the number of participants in which an adverse event has occurred, and report of any adverse events attributed to either of the conditions.

##### Service use

Although differences in service use are not formally hypothesised as an outcome of the intervention, a resource use questionnaire (RUQ) is administered in order to assess for any differences in mental health service utilisation between the groups before, during, and following intervention. This will be used to derive costings for the economic analysis. The RUQ was modified for the local context of the study, assessing use of mental health services in Victoria including hospital admissions (number and days) and consultations with mental health service providers (number and length). This will be supplemented by Australian Government Medicare data: these administrative data are complete, but do not include the full spectrum of services which participants in this study are likely to use.

#### Process variables

##### Self-stigma

Self-stigma will be measured by the Internalised Stigma of Mental Illness Scale (ISMI), a psychometrically validated self-report measure with 29 4-point *strongly agree* to *strongly disagree* items which provide a total, and separate scores for Alienation, Stereotype Endorsement, Discrimination Experience, Social Withdrawal and Stigma Resistance [45].

##### Self-efficacy

Self-efficacy for personal recovery is measured by the item “How confident are you that in the future you will be able to live a satisfying life alongside any mental health problems you may have” rated from 0 (*not confident I can do this at all*) to 100 (*highly confident I can do this*). Also included, using the same response scale, are a self-efficacy for illness self-management item (“How confident are you that you can do things to manage any future mental health difficulties”), and a series of 12 items relating to content of the website. A 0–100 rating of confidence in achieving full clinical recovery is also administered to assess discrimination from this construct. To assist with validation of this new measure, the widely used Generalised Self-Efficacy Scale (GSES [69]) is also completed.

#### Covariates and moderating variables

Demographics collected include age, gender, employment, education, country of birth and ethnicity. Clinical variables include SCID diagnosis, age at first specialist mental health service contact, past psychiatric admissions, and past receipt of psychiatric treatment on an involuntary basis. Ratings are also obtained of level of independent use of the Internet and email (each rated as use without assistance, use with occasional assistance, use only with assistance); frequency of use of the Internet, email, and social media; and membership of mental health related forums or social networks. Additionally the following variables are collected:

##### Recovery style

Recovery style refers to individual differences in adaptive coping during recovery from psychosis, which range from an *integrative* style in which the person approaches their psychotic experiences with curiosity and interest, to a *sealing over* style in which they are encapsulate their psychosis and see it as separate [70]. Past studies have suggested that persons with a sealing over style benefit less from interventions that involve discussion of mental health [71] making this a likely moderator of outcome. This will be measured using the Recovery Style Questionnaire, a self-report measure of 39 true/false items with good psychometric properties [72].

##### Mental health peer contact and identification

Because the intervention is primarily based upon peer delivery, its effects may be influenced by the extensiveness and quality of prior peer contact, and the degree to which the person identifies with mental health consumer peers. Positive peer contact is assessed using a brief description of experiencing a positive recovery from psychosis, to which the person indicates how many people they have encountered fitting this description on a 4-point ordinal scale. Peer group identification is assessed on a scale adapted from that of Watson et al. [73]. Items, rated on a 9-point scale from *not at all* to *very much*, ask the extent to which the person identifies with, feels strong ties with, and sees themselves as part of the group of people that might be referred to as mental health consumers/patients/service users; how often they think about themselves as part of this group; and how close they feel to other members of the group. Higher scores indicate greater group identification. The original adaptation of this scale has good internal consistency [73].

